#### 2.7.2. Secondary Outcomes

The secondary outcomes of this study include the early interruption rate; the withdrawal period (including the early interruption rate due to AEs of CTCAE grade 3 or above); the incidence of adverse drug reactions (ADRs, including irAEs for atezolizumab monotherapy and combined therapy [30,32,33] at CTCAE grade 3 or above with an incidence rate of over 1%); fatigue symptom improvement using the Functional Assessment of Chronic Illness Therapy—Fatigue domain (FACIT-F; Trial Outcome Index (TOI)—Fatigue) [34], the European Organization for the Research and Treatment of Cancer Quality of Life Questionnaire (EORTC-QLQ-C30) fatigue subscale [35,36,37], and the numeric rating scale (NRS) for fatigue; evaluations of skeletal muscle loss (using the strength, assistance with walking, rising from a chair, climbing stairs, and falls (SARC-F) questionnaire [38], a body composition test, the sit-to-stand test, and the thoracic muscle index), changes in the ECOG PS, pattern identification diagnosis, and treatment compliance. Demographic information such as age, sex, medical history, and laboratory tests will also be recorded.

Early discontinuation will be defined as failure to complete the planned study administration protocol regardless of the cause or dosing regimen, except when discontinuation is due to progressive disease. In addition, even if the planned three-cycle schedule has been completed, if the actual number of ICI doses during the treatment period is less than 60% of the total planned number due to toxicity, these patients will be included in the category of early discontinuation. To investigate therapeutic effects based on pattern identification, the cold–heat pattern identification questionnaire will be used to differentiate cold, non-cold, heat, and non-heat type classifications. This questionnaire consists of a five-point scale with 15 questions evaluating cold and heat types [39,40].

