### 2.9. Statistical Analysis

All statistical analyses will be performed using a two-tailed test with a 5% level of significance. An independent statistician will conduct statistical analysis using SAS^®^ Version 9.4 (SAS Institute Inc., Cary, NC, USA). 

The primary efficacy variable will be summarized using the full analysis set (FAS), and the per-protocol set (PPS) will be used for a supportive analysis. All other efficacy analyses will be based on the FAS. Safety variables will be summarized using a safety set (SS), which includes all participants receiving at least one dose of the study medication. The FAS will consist of all randomized participants who received at least one dose of the study medication and who underwent a valid measurement of the primary efficacy variable at baseline.

The PPS will consist of all participants in the FAS who showed no important protocol deviation affecting the primary efficacy variable.

Participants showing important protocol deviations will be predefined and evaluated during a data evaluation meeting prior to unblinding the data.

Categorical data will be presented as frequencies and percentages, and continuous data will be presented as means and 95% confidence intervals. 

The normality of continuous variables in the clinical data will be tested using the Kolmogorov–Smirnov test. Continuous data will be analyzed using the independent t-test or Wilcoxon rank-sum test, and categorical data will be analyzed using the chi-squared test or Fisher’s exact test for comparison of two groups. Mixed-effect model repeated measures (MMRM) will be used, with each group and visit time as fixed factors and subjects as random factors. Paired *t*-tests or Wilcoxon signed rank tests will be used to compare the factors before and after treatment. 

Pearson’s correlation or Spearman’s rank correlation tests will be used for each administration group in order to examine the correlations among various immune indicators measured in blood samples, treatment responses, and each identified pattern. The data collected in this study will be used as is for analysis without replacing or imputing missing values. 

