The findings of our study will provide basic evidence regarding the safety and efficacy of BJIKT in the treatment of patients with advanced NSCLC who are being treated with ICIs through a rigorously well-designed clinical trial. In addition, we will explore the therapeutic effects based on pattern identification, the most important factor for diagnosis and treatment in clinical fields [48,49,50,51,52].

However, this clinical trial is limited in that the survival benefits of combination therapy will not be evaluated due to the short trial period, and it will be conducted with a small sample size, so further clinical trials with large sample sizes need to be conducted to confirm safety and therapeutic effect of the coadministration of ICIs and BJIKT.

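### The correlations planned within each arm cannot show whether the BJIKT effect depends on cold/heat pattern, which the article says it will explore

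*Protocol article*

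**What the plan says.** Section 2.7.2 introduces the cold–heat questionnaire with a purpose: "To investigate therapeutic effects based on pattern identification". The Discussion repeats it: "we will explore the therapeutic effects based on pattern identification, the most important factor for diagnosis and treatment in clinical fields".

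Section 2.9 brings pattern and response together in one sentence, which applies Pearson or Spearman tests "for each administration group in order to examine the correlations among various immune indicators measured in blood samples, treatment responses, and each identified pattern". Between-arm methods in the same section are t-test or Wilcoxon, chi-squared or Fisher, and a mixed model described as follows: "Mixed-effect model repeated measures (MMRM) will be used, with each group and visit time as fixed factors and subjects as random factors". None has a pattern term. The section names no interaction, no contrast within pattern classes and no comparison of the two arms' correlations.

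Pattern also appears among the secondary outcomes ("changes in the ECOG PS, pattern identification diagnosis, and treatment compliance"). Table 1 schedules it at screening, V1 and V3.

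**The concern.** In a placebo-controlled trial the therapeutic effect of BJIKT is a difference between arms. Asking about that effect by pattern means asking whether the difference changes with pattern. A correlation within one arm answers another question: whether pattern and outcome go together among patients who all had the same treatment.

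The two answers can diverge in both directions. If pattern predicts outcome whatever the patient takes, both arms have a correlation and the BJIKT effect is the same for everyone. If pattern predicts outcome on placebo and BJIKT removes the gradient, the BJIKT arm shows nothing although its effect depends on pattern. Setting a significant result in one arm beside a non-significant one in the other does not help, because that is not a test of the difference between them. At stake is whether the pilot passes on a pattern-specific signal that its analysis cannot support.

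**Working it through.** **Inputs.** 30 patients, 15 per arm (section 2.8), and two-sided 5% tests (section 2.9). The sample size rests on feasibility, so beyond 15 + 15 = 30 there is no plan figure to reproduce. The article gives no correlation between pattern and response; a range of 0 to 0.7 is assumed.

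**Planned test, per arm.** With n = 15, the correlation is significant when |r| exceeds t/√(t² + n − 2). With t = 2.160 on 13 df this is 2.160/√(4.667 + 13) = 0.514.

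**Test that matches the aim.** With b the slope of outcome on pattern score in each arm, t = (b_BJIKT − b_placebo)/√[s²(1/Sxx_BJIKT + 1/Sxx_placebo)], where s² = (SSE_BJIKT + SSE_placebo)/26 and df = 30 − 4 = 26.

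**Purely prognostic pattern.** The true correlation is the same in both arms and there is no effect modification (40,000 simulated trials per row, continuous score and outcome):

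| r in both arms | BJIKT arm significant | BJIKT only | Both arms | Interaction test |
|---|---|---|---|---|
| 0 | 5.1% | 4.8% | 0.3% | 5.0% |
| 0.3 | 19.7% | 15.9% | 3.9% | 5.2% |
| 0.4 | 32.5% | 22.1% | 10.4% | 5.0% |
| 0.5 | 50.3% | 25.0% | 25.3% | 5.1% |
| 0.6 | 70.0% | 20.9% | 49.1% | 5.1% |
| 0.7 | 87.5% | 10.7% | 76.8% | 5.1% |

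The arms are independent, so the BJIKT-only column can be checked as P(BJIKT significant) × P(placebo not significant). At r = 0.5 this is 0.503 × (1 − 0.504) = 0.249; at r = 0.3 it is 0.197 × (1 − 0.194) = 0.159. Both agree with the simulation.

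**Two-level pattern** (7 versus 8 patients in each arm). With a prognostic difference of 0.8 or 1.0 SD in both arms, BJIKT-only significance occurs in 21.0% or 24.5% of trials, and the interaction test rejects in 4.8% or 5.0%. The result does not depend on a continuous score.

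**Pattern matters only under BJIKT** (placebo r = 0). BJIKT-only significance occurs in 18.8% (r = 0.3), 47.4% (0.5), 66.7% (0.6) and 83.4% (0.7). At r = 0.3 this is close to the 15.9% seen with no modification at all, so the picture from the separate arms hardly discriminates. The interaction test has 12.1%, 26.0%, 37.2% and 50.1% power.

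**BJIKT removes a placebo gradient** (BJIKT r = 0, placebo r = −0.5). The BJIKT-arm test rejects in 5.0%, the placebo-arm test in 50.6% and the interaction test in 26.1%.

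**Opposite gradients** (+0.5 and −0.5). Each arm's test rejects in about 50%; the interaction test rejects in 78.4%.

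**The case against.** The strongest reply is that the documents make no wrong claim. Section 2.9 says only that correlations will be examined. A reader might infer that the trial will present a correlation in the BJIKT arm as a BJIKT effect, but no sentence says so. Both arms are analysed, so a similar placebo gradient would often be visible. This stands: misreading is a risk, not a stated intention.

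A reader might also take the 20% to 70% rejection rates in the BJIKT arm (r = 0.3 to 0.6) as false-positive rates. They are not. A real within-arm correlation exists in those scenarios and the test is right to find it. Counting trials with either arm alone significant would also overstate the problem, since only BJIKT-only significance suggests a BJIKT benefit. Likewise, 5% rejection in the BJIKT arm when BJIKT removes a gradient does not mean the signal is lost, because the placebo arm is tested too.

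The consequence is limited as well. The three numbered aims in the Introduction are safety, symptom improvement, and feasibility through immune status and response rate; pattern is in none of them. The Discussion's verb is exploratory. Section 2.9 does not define treatment response, which may mean tumour response rather than fatigue. The article condenses a longer protocol, so the choice of visit for the pattern value may properly sit there, and its absence here is no error.

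What the reply does not remove is the mismatch. Two sections announce therapeutic effects by pattern, and the one method the article fixes for relating pattern to response has no contrast between arms. That holds whichever response is meant, and it concerns a method that is stated, not one that is left out.

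**Conclusion.** The point holds as a minor one. The named analysis describes association within each arm and does not answer the announced question about the BJIKT effect by pattern. With a purely prognostic pattern, significance under BJIKT alone would occur in about 16% to 25% of trials, against about 5% for an interaction test. This rests on assumed correlations of 0.3 to 0.6, equal in both arms, and on complete data for 15 patients per arm; section 2.9 excludes imputation, so actual numbers may be lower.

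Two stronger readings are not supported: that the plan intends to claim pattern-specific benefit from these correlations, and that correlation is its only use of pattern. Pattern diagnosis is also a secondary outcome, to which the general two-group tests can apply.

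**What to change.** Keep the correlations within arms as descriptive and state that they will not be used to claim a pattern-specific BJIKT effect. Then do one of the following.

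- Add an exploratory model on all FAS patients for a small number of key fatigue and muscle outcomes, with arm, pre-treatment outcome value, screening pattern score and arm-by-score interaction. Report the interaction with a 95% confidence interval. Use only the screening score as modifier, because V1 and V3 values may already have been changed by treatment; those remain outcomes.
- Or reword sections 2.7.2 and 3 so that they promise association only.

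The cost is a few lines of text and code. The questionnaire is already scheduled at screening, so no new data are needed. The drawback of the model is precision: interaction power is about 12% to 50% when pattern predicts outcome only under BJIKT at r = 0.3 to 0.7. The result is an estimate with a wide interval, not a confirmatory test. Limiting the number of outcomes avoids a long list of exploratory interactions.

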### 2.10. Data Management and Monitoring

Clinical trial monitoring will be conducted through regular site visits and telephone calls by a clinical research associate (CRA) on the monitoring committee in order to monitor protocol compliance, the recruitment rate, document reporting, and AEs during the trial period. If any problems arise during the clinical trial process, the CRA will consult with the investigator. 

The trial data will be saved in an electronic data capture system (Medidata Rave; Medidata Solutions Inc., New York, NY, USA) used for data collection and verification. The trial data will be managed by an independent data management (DM) team. The electronic CRF is accessible only to investigators who are directly involved in the clinical trial and receive relevant education. The range of the data values will be set in advance to ensure the data quality, and data entry will be performed only once by the investigators at the affiliated institutions. Data quality will be managed through two validation processes by the CRA and DM team. All data and documents obtained from the clinical trial will be preserved in a separate storage location. No information will be released without the permission of the principal investigator, and all data acquired during the trial will be stored separately in accordance with institutional review board (IRB) regulations.

### 2.11. Ethics and Dissemination

This study was approved by the IRB of Korea University Guro Hospital (approval number: 2021GR0472), Asan Medical Center (approval number: S2021-2096-0001), and Kyung Hee University Hospital (approval number: KHUH2021-08-079-001) on 30 September 2021. The trial was registered with the Clinical Research Information Service (https//cris.nih.go.kr/cris; identifier number, KCT0006689, accessed on 28 October 2021) in October 2021. This study is based on version 5.2 of the protocol. This is an ongoing trial. Recruitment started on 25 March 2022 and will be expected to be completed by 30 June 2023. 

All patient participation will be considered voluntary, and patients will be informed in advance that they can withdraw from the study at any time without penalty or adverse consequences. 

## 3. Discussion

Herein, we reported a study protocol for a pilot multicenter, randomized, double- blinded, placebo-controlled study assessing the safety and efficacy of BJIKT in advanced NSCLC patients concomitantly treated with ICIs. In addition, we will evaluate the feasibility of an integrative cancer treatment strategy by examining immune profiles and treatment responses to combined treatment with ICIs and herbal medicine.

ICIs have emerged as front-line therapeutic option for advanced NSCLC [4]. However, ICIs are reported to be associated with several AEs, including irAEs, that affect treatment discontinuation [5,6,7,8,9,10,11]. Fatigue is one of the most common AEs associated with ICI treatment in patients with lung cancer [6,9,10]. Furthermore, fatigue is a common symptom in advanced NSCLC, and patients with stage IV disease experience fatigue and weight loss at a higher rate than those at lower stages; thus, such symptoms and progression are more likely to occur in advanced-stage lung cancer [41]. Moreover, cancer-related fatigue (CRF) and loss of skeletal muscle in cancer patients are known to result from systemic inflammation [7,42,43,44]. However, maintenance of skeletal muscle through exercise is the only solution to this, as no active treatment plan has been proposed thus far [45,46,47]. In this regard, BJIKT can be considered a treatment alternative for the symptoms of fatigue and decreased skeletal muscle mass in cancer patients.

BJIKT is an herbal formula approved by the Korean MFDS as a medicine for weak constitution, tiredness, weakness after illness, anorexia, and night sweating. BJIKT exerts beneficial effects on CRF and quality of life in patients with cancer [13]. 

Moreover, BJIKT treatment has been shown to inhibit the production of proinflammatory cytokines and is considered a beneficial treatment for restoring the immunological status of cancer patients experiencing physical and psychological stress [14,15,16,17]. In addition, BJIKT enhances weakened immune function and suppresses the enhanced immune function attributable to the inflammatory response, suggesting that this medicine has a bidirectional immunomodulatory effect that compensates for both excess and deficiency conditions [18,19,20]. Although several studies have reported on the safety of BJIKT [21,22,23,24,25,26,27,28,29], none has evaluated the irAEs of BJIKT in patients with advanced NSCLC treated with ICIs.

The findings of our study will provide basic evidence regarding the safety and efficacy of BJIKT in the treatment of patients with advanced NSCLC who are being treated with ICIs through a rigorously well-designed clinical trial. In addition, we will explore the therapeutic effects based on pattern identification, the most important factor for diagnosis and treatment in clinical fields [48,49,50,51,52].

However, this clinical trial is limited in that the survival benefits of combination therapy will not be evaluated due to the short trial period, and it will be conducted with a small sample size, so further clinical trials with large sample sizes need to be conducted to confirm safety and therapeutic effect of the coadministration of ICIs and BJIKT.

## 4. Conclusions

This trial will be the first study to evaluate the safety and feasibility for ICIs and BJIKT as an integrative cancer treatment in advanced NSCLC patients. This study will provide basic evidence for the safety profiles, including irAEs, of herbal medicine in patients with advanced NSCLC who are being treated with ICIs. Hopefully, the findings of our study will provide basic evidence for further integrative research aimed at the survival benefits of combined treatment with ICIs and herbal medicine.

## Figures and Tables

**Figure 1 ijerph-20-04507-f001:**
[figure not shown]
Study flowchart. BJIKT, *Bojungikki-tang*; AE, adverse event; irAEs, immune-related adverse events; FACIT-F, Functional Assessment of Chronic Illness Therapy for Fatigue; NRS, Numeric Rating Scale; SARC-F, strength, assistance with walking, rising from a chair, climbing stairs, falls; SIT, sit-to-stand; QoL, quality of life; ORR, objective response rate.

**Table 1 ijerph-20-04507-t001:** Schedule of enrollment, interventions, and assessments.

	Study Period				
	Screening	Treatment & F/U			
		Baseline	V1	V2	V3 ^c^
Time Point	~4 Weeks	C1D1 (±7 Days)	C2D1 (±7 Days)	C3D1 (±7 Days)	C3D21 (±7 Days)
**Enrollment**					
Informed consent	X				
Eligibility screen	X	X			
Demographic characteristics	X				
Medical history	X	X			
PD-L1 testing (immunohistochemistry), EGFR/ALK mutation test	X				
Physical examination and vital signs	X	X	X		X
Electrocardiography	X				
ECOG PS	X	X	X		X
Random allocation		X			
**Interventions**					
Arm 1: atezolizumab + BJIKT					
Arm 2: atezolizumab + placebo					
**Assessments**					
EORTC-QLQ-C30	X		X		X
Fatigue subscale/NRS	X		X		X
FACIT-F(TOI-F)	X		X		X
SARC-F	X		X		X
Muscle test (InBody^TM^, STS test)	X		X		X
Cold/heat pattern	X		X		X
Laboratory testing ^a^	X	^b^	X		X
Immunological testing (blood collection)	X	^b^			X
Chest CT	X				X
X-ray examination		X	X	X	
Body composition test ^d^		X	X	X	X
Tumor evaluation (according to RECIST v1.1)	X				X
Adverse events (CTCAE v4.03)		X	X	X	X
Medication compliance			X	X	X

^a^ Hematological, blood biochemical, CRP, urine, and pregnancy testing. ^b^ Execute if necessary, according to the investigator’s judgment. ^c^ End of treatment (EOT). ^d^ Body weight, body fat percentage, body fat mass, skeletal muscle mass; ALK, anaplastic lymphoma kinase; BJIKT, *Bojungikki-tang*; C, cycle; CRP, C-reactive protein; CT, computed tomography; CTCAE, Common Terminology Criteria for Adverse Events; D, day(s); ECOG PS, Eastern Cooperative Oncology Group Performance Status; EGFR, epidermal growth factor receptor; EORTC-QLQ-C30, European Organization for Research and Treatment of Cancer Quality of Life Questionnaire; FACIT-F(TOI-F), Functional Assessment of Chronic Illness Therapy for Fatigue; F/U, follow-up; NRS, Numeric Rating Scale; RECIST, Response Evaluation Criteria in Solid Tumors; STS, sit-to-stand; SARC-F, strength, assistance with walking, rising from a chair, climbing stairs, and falls questionnaire.

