## 2. Materials and Methods

### 2.1. Study Design and Setting

This multicenter, randomized, placebo-controlled pilot study will be performed at Korea University Guro Hospital, Asan Medical Center, and Kyung Hee University Hospital (all located in Seoul, Republic of Korea). A total of 30 patients with NSCLC scheduled to undergo second- and subsequent-line monotherapy with atezolizumab, an ICI, will be recruited after obtaining their written informed consent. The enrolled participants will be randomly allocated into two parallel groups: BJIKT (atezolizumab + BJIKT) and placebo (atezolizumab + placebo). Patients will receive intravenous atezolizumab (at a 1200 mg fixed dose) every three weeks on day 1 of each three-week cycle [30]. According to the allocated group, patients will take BJIKT or placebo (4 g at a time) every day, regardless of withdrawal of the base drug, starting from the initiation of atezolizumab therapy. The trial will consist of three cycles administered over the course of approximately nine weeks, with a screening period and three study visits at three-week intervals. All participants will undergo the necessary examinations and testing procedures within four weeks prior to enrollment (i.e., prior to administering the investigational drug) according to the described clinical trial protocol.

The study period procedure is summarized in the Consolidated Standards of Reporting Trials (CONSORT) diagram (Figure 1), and this protocol is written in accordance with the recommendations of the Standard Protocol Items: Recommendations for Interventional Trials (SPIRIT) checklist. The schedule of enrolment, intervention, and assessments is summarized in Table 1.

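### The fatigue scales, SARC-F and sit-to-stand test are not measured at C1D1, so within-arm before/after tests count up to four untreated weeks as change on treatment

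*Protocol article*

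**What the plan says.** The rows of Table 1 that matter here read as follows.

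| Row | Screening | Baseline (C1D1) | V1 | V2 | V3 |
|---|---|---|---|---|---|
| EORTC-QLQ-C30; "Fatigue subscale/NRS"; FACIT-F; SARC-F | X | – | X | – | X |
| "Muscle test (InBody^TM^, STS test") | X | – | X | – | X |
| "Body composition test ^d" | – | X | X | X | X |
| ECOG PS; physical examination and vital signs | X | X | X | – | X |
| Random allocation | – | X | – | – | – |

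Section 2.1 sets the screening window: "All participants will undergo the necessary examinations and testing procedures within four weeks prior to enrollment", where enrolment is taken to mean the point before study drug is given. BJIKT or placebo starts together with atezolizumab.

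Footnote d to Table 1 defines the body composition test as "Body weight, body fat percentage, body fat mass, skeletal muscle mass". No footnote says what InBody records. Section 2.7.2 lists the muscle outcomes as SARC-F plus "a body composition test, the sit-to-stand test, and the thoracic muscle index", and does not name InBody.

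Section 2.9 plans between-arm tests, an MMRM with group and visit as fixed factors and no baseline covariate named, and within-arm tests: paired t-tests or "Wilcoxon signed rank tests will be used to compare the factors before and after treatment". It does not say which column of Table 1 is the baseline.

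**The concern.** Improvement in fatigue and muscle loss is the second of the three aims in the Introduction, and these scales carry it. A before/after test has a clear meaning only if the first value is taken when treatment starts. Here it can be four weeks earlier, in patients whose disease has progressed during or after platinum chemotherapy. Fatigue can move either way in that time. It may worsen with the disease. It may also ease as earlier toxicity settles, since exclusion criterion 15 judges unresolved toxicity at the start of trial therapy. Easing before the first dose would look like improvement on BJIKT.

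A second possible cost is precision. If an older value correlates less with the outcome, change scores or baseline adjustment gain less from it, and there are only 15 patients per arm.

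The visit itself is not the obstacle: ECOG PS and the physical examination are repeated at C1D1.

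**Working it through.** The plan has no power calculation to reproduce. Section 2.8 sets 30 patients (15 per arm) on feasibility.

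**1. Untreated share of the interval.** Inputs: a screening lead of up to 4 weeks (Section 2.1; Table 1); V1 about 3 weeks and V3 about 9 weeks after C1D1 (Section 2.1). Share = lead / (lead + weeks on treatment).
- Lead 4 weeks: to V1, 4/(4+3) = 57%; to V3, 4/(4+9) = 31%.
- Lead 1 week: to V1, 1/4 = 25%; to V3, 1/10 = 10%.

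**2. Effect on the tests.** Simulation of 20,000 trials with 15 per arm, no treatment effect, an assumed pre/post correlation of 0.6, and the same assumed pre-treatment drift in both arms.

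| Drift (SD) | Mean between-arm difference in change (SD) | Between-arm rejection | Within-arm paired rejection |
|---|---|---|---|
| 0 | 0.003 | 4.9% | 4.9% |
| 0.25 | 0.000 | 5.1% | 17% |
| 0.5 | 0.003 | 5.1% | 52% |

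The within-arm figures can be checked from the noncentrality, drift × √15 / √(2(1−0.6)). The SD of the change is √0.8 = 0.894, which gives 0.25 × 3.873/0.894 = 1.08 and 0.5 × 3.873/0.894 = 2.17. Both agree with the simulated rates.

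**3. Between-arm precision.** The document gives no correlation ρ between the pre-treatment value and the outcome, so these are assumed values. With unit SD, the variance of a change score is 2(1−ρ), and the residual variance after baseline adjustment is 1−ρ².
- ρ unchanged: ratio of standard errors 1.00, no loss.
- ρ from 0.7 (measured at C1D1) to 0.6 (measured at screening): change score √(0.8/0.6) = 1.155; adjusted √(0.64/0.51) = 1.12. The standard error is 12–15% larger. By normal approximation, power for a 0.8 SD difference goes from 81% to 69% (change score) or from 87% to 78% (adjusted).

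As a plausibility check, suppose ρ is 0.7 over nine weeks and decays exponentially with time. The full four-week lag then gives 0.7^(13/9) = 0.60, so 0.6 is about what this decay implies at the maximum lead.

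**4. Muscle mass.** Only the body-composition row is stated to contain skeletal muscle mass, and it has a C1D1 value. The InBody row has a different pre-treatment visit and no V2. If InBody also yields muscle mass, which the article does not say, the two rows overlap on different schedules.

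**The case against.** A pre-randomisation screening value is a legitimate baseline, and Table 1 is consistent with the window in Section 2.1. This is therefore a design choice and not a contradiction. Four weeks is the maximum, and a screening close to C1D1 makes the issue small. The outcomes are secondary in a pilot, and the primary adverse-event outcomes are untouched. A definition of baseline may stand in the full protocol or analysis plan. All of this is fair. It limits the weight of the point but does not remove it: the assessment schedule is protocol content, and no analysis plan can supply a C1D1 measurement that was not taken.

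Three stronger readings are tempting, and the documents do not support them.
- *The treatment comparison is biased.* It is not. Screening precedes allocation, and both blinded arms share the same window, so drift cancels in expectation. The simulation shows this.
- *The stale baseline leaves the equivalent of about 20 of 30 patients.* That needs ρ to fall from 0.7 to 0.5 (30 × 0.51/0.75 = 20.4). Under the exponential decay above, 0.5 is reached only after about 17.5 weeks, a lag of about 8.5 weeks and well outside the window. The figure also presumes a baseline covariate that Section 2.9 does not name.
- *Skeletal muscle mass has two conflicting baselines.* Footnote d attaches it to one row only. The relation between the two rows is unclear, but a contradiction is not shown.

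**Conclusion.** The point holds for the within-arm analyses. The fatigue scales, SARC-F and sit-to-stand test have no value at treatment start, so a before/after test mixes untreated change with change on treatment. At the maximum lead the untreated part is 57% of the interval to V1 and 31% of the interval to V3. How far this inflates rejection depends on a drift that the document does not give: about 17% at 0.25 SD and 52% at 0.5 SD, with ρ = 0.6, against a nominal 5%.

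For the between-arm comparison, only precision is at issue. The loss runs from none, if the correlation does not decay with lead time, to a standard error 12–15% larger if it falls from 0.7 to 0.6. The two muscle rows are an ambiguity to clear up. The correction is worth making for the trial's second aim; it has no bearing on the primary outcomes.

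**What to change.** - In Table 1, schedule EORTC-QLQ-C30, the fatigue NRS, FACIT-F, SARC-F and the sit-to-stand test at C1D1 before the first dose, and use that value as baseline.
- For patients already enrolled, keep the screening value as baseline and record its lag to C1D1 in days.
- State that within-arm change from a screening baseline is not to be read as a treatment effect.
- Explain how the InBody row (screening, V1, V3) relates to the body-composition row (Baseline, V1, V2, V3), and name the C1D1 body-composition value as the skeletal muscle mass baseline.

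The cost is a minor amendment at three sites, and a few questionnaires and a chair test at a visit already held. The downside is two baseline types within 30 patients, which must be flagged in the data. Recruitment is due to end by 30 June 2023, so few patients may gain a C1D1 value. The recorded lag and the stated baseline remain useful even if none does.
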